## Methods/design

### Study design

This will be a randomised controlled trial where 200 patients with HF will be randomised to receive either: 1) the Virtual Week Training Program, a computerised adaptively difficult PM training program, or 2) non-adaptive computer-based word puzzles. Sixty healthy control participants, with no HF diagnosis, will also be assessed to compare differences in baseline measures of cognitive and psychosocial functioning. There are 4 phases to the study: 1) baseline testing; 2) 6 weeks of cognitive training; 3) Assessment One, 2 to 4 weeks post cognitive training; and 4) Assessment Two, 12 months post cognitive training. There will be two separate interviews during each of the assessments (baseline testing, Assessment One and Assessment Two). These will be: a) nursing assessment including physical functioning, and self-care; and b) PM and neurocognitive assessment, and TIADL.

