### Participant inclusion criteria

A total of 200 HF patients aged 18 years or older will be recruited. Inclusion criteria will be: diagnosis of HF with reduced ejection fraction (ejection fraction < 45% in the previous 2 years) as confirmed by a cardiologist and consistent with Australian guidelines [34]; attendance at a specialist HF clinic or rehabilitation program, and/or a disease management program with nursing follow-up and able to participate in the study (that is adequate vision, hearing and English comprehension). Carers will be identified by HF patients as someone who is familiar with and contributes to the management of their heart condition (for example, a partner, family member, friend or next of kin). Patients who cannot identify a carer will still be eligible to participate in the study. All HF patients enrolled in the study will continue to receive usual care which can be from any combination of nurse-led chronic disease management programs, specialised HF outpatient clinics, or outpatient rehabilitation programs. A key aspect of usual care is patient education and support from a multidisciplinary team that is directed at promoting self-care maintenance and monitoring behaviours. Healthy control participants will be living independently in the community without a medical diagnosis of HF and have adequate performance on the Addenbrooke’s Cognitive Examination Revised (ACE-R) [35].

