### Participant exclusion criteria

Patients will be excluded if they: do not have access to a PC computer; do not have basic computer skills or do not have the physical ability to use a computer keyboard; reside in a long-term high-care facility (nursing home); have a documented history of moderate-to-severe cognitive impairment or dementia, a cerebrovascular accident, acute myocardial infarction or have undergone cardiac surgery in the previous 3 months; or have a terminal diagnosis. Carers will be excluded if they have a documented history of moderate-to-severe cognitive impairment or dementia or have a terminal diagnosis. Healthy control participants will be excluded if they: reside in a long-term high-care facility (nursing home); have moderate-to-severe cognitive impairment or dementia; or have experienced a cardiac event within the past 6 months (cerebrovascular accident, acute myocardial infarction or cardiac surgery).

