### Baseline and follow-up measures to be collected from all HF patient participants

A comprehensive baseline assessment of HF patients will be conducted prior to randomisation and the first intervention session. The baseline assessment will include socio-demographic, psychosocial, cognitive and clinical profiling using a combination of self-report and review of patient records. Table 1 displays baseline, 4-week and 12-month assessments. The following measures will be administered during the assessment:

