
In a second interview, HF patients will undergo comprehensive PM and neurocognitive assessment, and TIADL, which will take 90 to 120 minutes to complete. The second interview will include the following:I.*Global cognitive screen*. The Addenbrooke’s Cognitive Examination Revised (ACE-R), a sensitive cognitive screening test of global cognitive functioning [35], measures 5 cognitive domains; attention/orientation, memory, verbal fluency, language and visuospatial abilities. Lower scores suggest poor cognitive performance. ACE-R is sensitive to early stages of dementia [51] and will be used as a participant screen. Adequate performance on the ACE-R is required for the participant’s data to be included in the final data sample.II.*Prospective memory* (*PM*). There will be a rigorous assessment of PM.The *Memory for Intentions Screening Test* (*MIST*) [52] is a standardised measure of PM developed for use in clinical settings. Throughout the test, participants will be required to remember and perform 4 time-based (for example; ‘in exactly 15 minutes please tell me it is time to take a break’) and 4 event-based tasks (for example: ‘when I hand you a red pen, please sign your name on the paper’). A series of word search puzzles will be provided as a distractor task to prevent overt rehearsal of the prescribed intentions. The researcher will monitor whether the participant remembers to perform the PM tasks correctly. Errors and scoring will be assessed in accordance with the MIST professional manual, which allows for an assessment of eight differing aspects of PM functioning. The MIST takes 30 minutes to administer. Total scores range from 0 to 48 with higher scores indicating better performance on the task. The MIST is sensitive to various neurological disorders, such as mild cognitive impairment [53] and has good reliability and validity [54].The brief *Virtual Week assessment*, which involves 2 ‘virtual’ days of the computerised board game, will assess event-based and time-based PM tasks. Based on our previous study with HF patients [55], the brief version of Virtual Week will take 30 to 45 minutes to complete.The *Naturalistic PM task* assesses 2 types of time-based PM tasks: 1) an appointment task at a set time of day and 2) one requiring monitoring a short interval of time. The latter is typical of many laboratory-based PM tasks. Participants will be asked to ring a prescribed number at 2 set times over 3 consecutive days. With each scheduled phone call, a recorded message will ask participants to call back after an interval of 5, 10 or 20 minutes.III.*Timed Instrumental Activities of Daily Living* (*TIADL*). Participants’ level of independence in daily activities will be assessed using a modified version of the TIADL [56]. Participants are required to complete nine activities that are relevant to tasks they would perform at home. The original five tasks are functional measures basic to independent living such as telephone communications, financial abilities, nutrition, shopping and medication use. Four additional tasks that are more relevant in the current technological communication environment and specifically related to HF self-care have been adapted for this study: 1) checking and sorting the sodium content of 3 food packages from the lowest to the highest amount of sodium; 2) extracting health information from a computer screen simulating a webpage to estimate a target heart rate for exercise; 3) extracting data from a webpage to look up a specified train timetable, and 4) finding a matching pair of black socks in a laundry basket full of mixed single socks. Participants are scored on the length of time to complete each of the nine activities, and if any, the type of error in performing the activity. Shorter completion times indicate better performance. The rapid and efficient completion of these tasks is advantageous in daily life and the time taken to complete the tasks is an objective indication of functional independence [56]. This assessment will be a key strength to the study, providing an objective and sensitive behavioural measure to evaluate the effectiveness of the cognitive training intervention on everyday functional independence.IV.*Working memory and executive functioning*. A battery of tests from the CogState program will be used (www.cogstate.com) [57,58]: i) The One Back Task assesses working memory. Participants are presented with a succession of playing cards on a screen and must decide if the card displayed is the same as the one presented immediately before; ii) The Two Back Task is presented in the same way as the One Back Task: however, participants are required to decide if the card displayed on screen is the same as a card presented two cards previously. Responses that are more accurate reflect better working memory, on both tasks; iii) The Detection Task measures psychomotor functioning and speed of processing. Participants must respond as quickly as possible to a card flipping over on screen, by pressing a button on the keyboard. Reaction time is measured and lower scores indicate better performance; iv) The Identification Task measures visual attention. Participants must decide whether a playing card presented on screen is red, by pressing the ‘Yes’ or ‘No’ button. Reaction time is measured and lower scores indicate better performance; v) The One Card Learning Task measures visual learning and memory. Participants are presented with a succession of playing card on screen, and must decide if the card currently displayed has been displayed previously. Accuracy of performance is measured, with higher scores indicating better performance. In addition to the computer battery of tests that take only 8 minutes to complete, there will be a pen and paper task, the Trail Making Test (TMT) [59], which assesses planning ability. It consists of two parts: Part A and B. In Part A, participants are required to draw lines to connect circles that are numbered consecutively; in Part B, participants connect circles that are numbered or lettered, alternating between the numeric and alphabetic sequences. This test takes approximately 5 minutes to complete, and the participant’s score is the total time taken to complete the task. Lower scores on the TMT indicate higher levels of planning ability.V.*Verbal memory*. In the Hopkins Verbal Learning Test-Revised [60,61], participants must listen to a list of 12 words read out by the experimenter, and then verbally recall as many words as possible from that list. This same procedure is repeated two more times. The participant is then asked, after a 20- to 25-minute interval, to verbally recall the same list of words. Following this final trial, the researcher reads out a list of 24 words and the participant is asked to identify the words that were presented in the original list of 12 words. This verbal memory test assesses episodic memory and the delayed recall test is particularly sensitive to ageing and abnormal ageing. The test has been successfully used in clinical and healthy populations of older adults [62].VI.*Premorbid intelligence*. The National Adult Reading Test (NART) [63] is a word-recognition test of vocabulary knowledge that requires participants to read aloud 50 English words of increasing difficulty that do not follow normal phonetic rules: for example, ‘chord’. This test takes about 5 minutes to complete and responses are audio-recorded for scoring purposes. The NART is widely used as an estimate of premorbid ability given the premise that reading ability is relatively independent of brain damage. Furthermore, NART performance appears to be impervious to the effects of many neurological and psychiatric conditions [64]. In a retrospective validity study of the NART, there was a strong correlation (*r* = 0.73; *P* < 0.001) between Intelligence Quotient (IQ) age 11 and NART performance at age 77 [64]. The NART will be used to characterise the HF sample and match the healthy non-HF controls on premorbid intelligence.

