### Outcomes

Primary study outcomes are patient engagement in HF self-care behaviours from both self-report (SCHFI) and the objective assessments from the carer, researcher and nurse, described above. Secondary outcomes are those not directly related to HF self-care behaviors but relevant to HF: quality of life; BNP, ‘Up and Go’ test, hospital readmissions, survival and transfer effects. To examine near to far transfer effects of the cognitive training we shall use PM tests aligned (or similar) to the training task, MIST and Virtual Week for near transfer effect. To examine for far transfer effects we will reassess overall cognitive function at Assessments One and Two. The TIADL and naturalistic PM task will assess transfer to everyday functioning, and will potentially represent somewhere between near and far transfer.

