### Randomisation and allocation concealment

Using CONSORT principles [71] HF patients will be randomised to 1 of the 2 study interventions: 1) usual care plus PM training (see Figure 1) or 2) active control group. Block randomisation will be allocated via a computer generated number prepared by an investigator with no involvement in data collection. Block randomisation with 1:1 ratio will be used to keep the 2 groups at similar sizes. Once the HF patient has consented to the study and baseline measures have been collected the research assistant will contact one of the training study investigators, who are independent of the recruitment process and data collection, for allocation consignment. Research assistants collecting baseline measures will not be informed of the patient’s assignment. Instead, the research assistant conducting the cognitive training will be notified when a patient has been randomised to this intervention. Participants enrolled in the study will be aware of the training activity they have been allocated and therefore they will not be blinded to the treatment allocation.

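### Patients' data are kept only if ACE-R performance is adequate, but ACE-R is neither an eligibility criterion for heart failure patients nor a stop before randomisation, so a randomised patient can be dropped

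*Protocol article*

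**What the plan says.** The rule stands in the protocol article under the baseline and follow-up measures for HF patients, second interview, item I (global cognitive screen): "Adequate performance on the ACE-R is required for the participant’s data to be included in the final data sample". The sentence before it gives the instrument's role: "ACE-R is sensitive to early stages of dementia [51] and will be used as a participant screen".

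Other sections bear on how the rule works:

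- **Participant inclusion criteria.** Only the healthy controls are required to "have adequate performance on the Addenbrooke’s Cognitive Examination Revised (ACE-R"). No such condition is set for HF patients.
- **Participant exclusion criteria.** The cognitive exclusion for HF patients is that they "have a documented history of moderate-to-severe cognitive impairment or dementia". It rests on the medical record, not on a test score.
- **Timing of baseline.** "A comprehensive baseline assessment of HF patients will be conducted prior to randomisation and the first intervention session".
- **Randomisation and allocation concealment.** The sentence on the trigger for allocation begins: "Once the HF patient has consented to the study and baseline measures have been collected the research assistant will contact one of the training study". Passing the ACE-R is not mentioned.
- **Study design.** "There will be two separate interviews during each of the assessments (baseline testing, Assessment One and Assessment Two"). The second interview, where the ACE-R is listed, is one of these two.
- **Table 1.** The ACE-R does not appear. The instrument shown as the cognitive screen, at all three time points, is the MoCA.

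**The concern.** The rule decides whose data are kept, not who may enter. Because neither the HF criteria nor the randomisation step applies it, the only place left for it to act is after a patient has been accepted. A patient with undocumented or mild impairment meets the criteria, consents, completes baseline, is allocated to an arm, and can then be taken out of the data.

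Two things are at stake. First, the comparison of training with word puzzles would no longer rest on all randomised patients, and the rule would affect every outcome. Second, aim 1 is to confirm cognitive deficits in HF patients relative to healthy controls. Removing HF patients with low ACE-R scores may restrict that group at the end where deficits lie.

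**Working it through.** **Step 1: can the rule be an eligibility rule as the text stands?**

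| Stage | What the article requires of HF patients | ACE-R involved? |
|---|---|---|
| Inclusion | HF with reduced ejection fraction, attendance at a HF service, able to take part | No (controls only) |
| Exclusion | Documented moderate-to-severe impairment, among others | No |
| Randomisation | Consent given, baseline measures collected | No stop for a failed score |
| Final data | Adequate ACE-R | Yes |

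The ACE-R is described as sensitive to early dementia, so it can flag patients whom a criterion based on documented moderate-to-severe impairment lets in. The set of randomised patients and the set of analysed patients can therefore differ.

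**Step 2: does the choice of time point matter?** A simulation illustrates this. All inputs are assumptions: 400,000 patients per arm, follow-up ACE-R correlated 0.7 with baseline, training effect on ACE-R of 0.3 or 0.5 SD, correlation of 0.3 or 0.5 between outcome and ACE-R, no true effect on the outcome, and a cut-off that fails 10% or 20% of controls.

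| Score used to exclude | Excluded, training arm | Excluded, control arm | Bias in outcome difference |
|---|---|---|---|
| Baseline | equal by design | equal by design | at most 0.007 SD in size (simulation noise) |
| Follow-up | 4% to 13% | 10% to 20% | -0.02 to -0.08 SD |

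A baseline score cannot depend on an arm not yet assigned, so zero bias is expected there. A follow-up score can differ by arm. Under these inputs it keeps more low performers in the training arm and biases against training.

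**Step 3: how many patients might be lost?** The article gives no ACE-R failure rate, so this is context only.

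- Approximation for two equal groups: power = Φ(d·√(n/2) − 1.96), two-sided α = 0.05, with d = 2f.
- The 63 per group in the Sample size section is reproduced at an assumed d = 0.5: 2 × (1.96 + 0.84)² / 0.5² = 62.7, rounded up to 63.
- After the stated 20% allowance, 100 × 0.80 = 80 per group. At d = 0.5: 0.5 × √40 − 1.96 = 1.20, power 88.5%.

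| Assumed ACE-R failures | n per group | Power, d = 0.5 (f = 0.25) | Power, d = 0.8 (f = 0.4) |
|---|---|---|---|
| 0% | 80 | 88.5% | 99.9% |
| 10% | 72 | 85.1% | 99.8% |
| 20% | 64 | 80.7% | 99.5% |
| 30% | 56 | 75.4% | 98.9% |

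The article writes its effect size as f² = 0.4, that is f = √0.4 = 0.63 and d = 1.26. Power there stays above 99.9% throughout. The point therefore does not rest on power.

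**The case against.** The strongest reply is that a pre-randomisation screen was meant. The article calls the ACE-R a screen, baseline comes before randomisation, and allocation is requested only after baseline measures are in. This is the more natural intention, and it removes any differential selection. It does not remove the inconsistency, because no section says that a patient who fails is not randomised, and the rule is worded as a condition on data.

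A reader might go further and infer that patients are dropped on a follow-up score, because the second interview recurs at all three assessments. The documents do not support this. The NART is in the same interview list, yet Table 1 marks it at baseline only, so being listed there does not show repetition. Table 1 schedules no ACE-R at any visit. The text does not rule out a follow-up ACE-R, but it does not plan one either.

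A reader might also infer that the ACE-R is a score the intervention targets. The training targets prospective memory, and the ACE-R is not a named outcome. The Outcomes section says "we will reassess overall cognitive function at Assessments One and Two" without naming the instrument, and repeated tests in Table 1 can supply that measure. Nor does any section say that staff who know the arm apply the rule: nobody is named as applying it, and those collecting baseline measures are not told the allocation.

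Three further limits stand. Impairment in up to 75% of HF patients, cited in the Background, is not an ACE-R failure rate in a sample that excludes documented moderate-to-severe impairment and requires computer skills. Controls must also pass the ACE-R, so aim 1 screens both sides, and the size of any truncation is unknown. The missing numeric cut-off is the kind of detail an article leaves to the full protocol, and would not be a finding alone.

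**Conclusion.** The point holds as an inconsistency about the analysis set. Followed literally, the article lets an eligible, randomised patient be removed from the data because of a test that is not part of HF eligibility.

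On the likelier reading, with only the pre-randomisation score used and the threshold set in advance, bias between arms is about zero. The harm is then discarded randomised patients, results that apply to a narrower population than the one enrolled, and a possible but unquantified restriction of the HF group in aim 1. Differential selection would need a follow-up ACE-R. Even then the illustrative bias is under 0.1 SD on assumed inputs. The number of patients affected cannot be derived from the article.

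This is more than a missing detail: the article states an affirmative rule that governs whose data enter every analysis, and that rule does not agree with the eligibility and randomisation sections. It should be settled before any analysis.

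**What to change.** Choose one of two wordings.

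1. **Eligibility.** Add adequate ACE-R performance to the HF-patient criteria, applied once at baseline, and state in the randomisation section that a patient who does not meet it is not randomised. Fix the threshold in advance, and delete the sentence about the final data. The Trial status section says recruitment is under way, so patients already randomised should be kept whatever their score.
2. **Analysis.** Replace the sentence with: *All randomised patients are analysed in their allocated group regardless of ACE-R score.* Exclusion on ACE-R may then be a sensitivity analysis, using the baseline score.

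Under either option, enter the ACE-R in Table 1 at the visits where it is given, and say whether the HF group in the aim 1 comparison is screened on the same rule as the controls.

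The cost is wording only, since the ACE-R is already among the listed measures. Option 1 brings some extra screen failures. Option 2 leaves a slightly more impaired analysed sample.

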
### Baseline and follow-up measures to be collected from carers

Carers will be asked to complete seven brief questionnaires:I.A health screening questionnaire will be used to identify the presence of specific health problems (cardiac, metabolic, diabetic, respiratory, muscular, family history, treatment precautions, and physical activity) and will be used for descriptive purposes.II.Carer contribution to HF self-care (CC-SCHFI) [65] is derived from the SCHFI and assesses the career’s contribution to self-care maintenance and management behaviours. This information will be used to provide a more comprehensive assessment of the patient participant’s engagement in self-care.III.Control Attitudes Scale - Revised (CAS-R) [41] will be administered to measure the carer’s perceived control in relation HF management. Each item is measured on a 5-point Likert scale ranging from 1 (strongly disagree) to 5 (strongly agree) and has been shown to have good internal reliability in a HF population (α = 0.76) [41]. This scale has been adapted for administration to the caregivers of patients with cardiac disorders [42,43].IV.Carers will also identify how their relationship with the HF patient functions in terms of managing HF symptoms using the dyadic HF care typology (described above).V.SF-12 will be administered (described above) as an indication of the quality of life of the carer.VI.Modified Caregiver Strain Index (MCSI) assesses the causes, and the degree of strain, and changes in strain over time. It has four domains of strain: financial, physical, psychological and social and personal. The reported internal reliability of the MCSI is high (Cronbach’s α = 0.90) and it correlates with care recipient’s functioning [66,67]. The tool will be administered to monitor changes in carer strain from baseline to 3- and 12-month follow-up.VII.To measure of HF patients’ level of functioning, carers will be asked to indicate the HF participants’ level of independence in daily activities using the validated Instrumental Activities of Daily Living (IADL) Scale [68]. This instrument assesses how much help the individual requires to perform each of eight tasks (using the telephone, shopping, food preparation, housekeeping, laundry, transportation, managing medications and home finances). A score of 1 indicates ‘no help’, and higher scores indicate increased dependence. Performing instrumental daily activities successfully requires a high level of skill and judgment: therefore, greater dependency is likely to be sensitive to mild changes in cognitive capacity [69].
